#### Teachers’ measures

Teachers will self-report their age, sex, teaching experience, type of school (public or private), and school location (rural or urban). It is important to note that, since some teachers’ responses may vary depending on the classroom group, teachers will need to complete the questionnaire with consideration of the specific student groups selected for the study.

##### Teacher interpersonal behavior

To assess teachers’ need-supportive and need-thwarting behaviors, the PE Spanish version of the Interpersonal Behaviors Questionnaire (Burgueño and Medina-Casaubón, 2021) will be adapted to teachers. The scale begins with the stem “In PE classes … “followed by 24 items (four items per factor) that measure autonomy (e.g., “… I encourage them to make their own decisions”), competence (e.g., “… I acknowledge their abilities to achieve their goals”), and relatedness support (e.g., “… I show interest in their activities”), as well as autonomy (e.g., “… I restrict their ability to make decisions”), competence (e.g., “… I question their ability to make progress”), and relatedness thwarting (e.g., “… I do not show interest in them”). It is important to note that although this study primarily focuses on supporting relatedness-supportive behaviors and avoiding relatedness-thwarting behaviors, we will also include autonomy- and competence-supportive/thwarting behaviors to control for their potential effects. Responses will be assessed using a 5-point Likert scale, ranging from 1 (*strongly disagree*) to 5 (*strongly agree*).

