### Class cohesion from the Conceptual Model of Cohesion

Cohesion was defined by Carron et al. (1998) as “a dynamic process that is reflected in the tendency for a group to stick together and remain united in the pursuit of its instrumental objectives and/or for the satisfaction of member affective needs” (p. 213). In the educational context, class cohesion refers to students’ collaboration in achieving shared academic goals and common social bonds (Leo et al., 2022). This class cohesion can be observed in two main dimensions: task cohesion, which pertains to students’ collaboration in academic activities, and social cohesion, which relates to the strengthening of interpersonal and affective bonds among students (Leo et al., 2022).

In this regard, teachers also play a fundamental role in facilitating class cohesion within the classroom. They can implement strategies to enhance both task and social cohesion through structured activities inside and outside the classroom, fostering collaboration among students. These strategies may include assigning interdependent roles, responsibilities, and tasks, as well as promoting peer communication, peer assessment with formative purposes, and social skills development. Moreover, establishing shared goals, designing challenges that require mutual support, and creating opportunities for students to engage in meaningful interactions, where they can express their interests, concerns, and motivations, help cultivate an integrated and participatory learning environment (Leo et al., 2023d).

Previous research indicates that students who perceive themselves as part of a cohesive group tend to exhibit higher values in key variables related to learning processes, such as students’ autonomous motivation and engagement (Leo et al., 2023a, 2023d, 2023e). Therefore, designing training programs focused on providing PE teachers with relatedness-supportive and class cohesion strategies could foster a warm environment that promotes students’ social interactions and improves learning-related outcomes.

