### Previous training programs focused on relatedness support and class cohesion

Previous SDT-based training programs among PE teachers have predominantly focused on how to provide autonomy support to students (Vasconcellos et al., 2020). Additionally, some SDT-based training programs among PE teachers have focused on both autonomy and competence support (Patzak and Zhang, 2025) or have simultaneously addressed all three basic psychological needs—autonomy, competence, and relatedness (Vasconcellos et al., 2020; White et al., 2021). Overall, the results from these studies indicate that teachers who participate in these training programs not only learn how to provide autonomy and competence support in their PE classes but also experience benefits, such as increased need satisfaction at work (Cheon et al., 2014, 2018; Tilga et al., 2021), relatedness satisfaction with their students (Reeve and Cheon, 2021), and greater job satisfaction (Cheon et al., 2014, 2020), among other positive outcomes. Additionally, students taught by trained teachers have demonstrated notable improvements in need satisfaction, need frustration, autonomous motivation and other (mal)adaptive outcomes in PE lessons (Vasconcellos et al., 2020; Reeve and Cheon, 2021). In contrast to these previous works, the present study focuses specifically on relatedness support, based on the premise that meaningful learning can be greatly facilitated through peer interaction within the classroom. Despite the recognized value of peer collaboration for learning and engagement, existing strategies to promote relatedness have typically been implemented alongside other strategies (i.e., autonomy support and competence support; Vasconcellos et al., 2020) and have rarely been applied in isolation (Sparks et al., 2017). As a result, the specific contribution of relatedness support strategies to students’ learning remains largely unexplored (Leo et al., 2023d). To address this gap, the present study integrates two complementary theoretical frameworks (i.e., SDT and CMC). This dual framework allows us to approach relatedness both as an individual psychological experience, in the context of teacher-student and student–student interactions (i.e., SDT), and class cohesion as a shared sense of connection among all classmates as a group (i.e., CMC), in line with the broader educational goal of fostering collaborative and socially rich learning environments.

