#### PE implementation for experimental group students

The implementation phase will last approximately 6 months, from October to the end of March, as we plan to conduct a post-intervention follow-up measure in the final month of the academic year (i.e., June; see Figure 1). During this period, the co-created strategies will be implemented by the experimental group teachers. Relatedness-supportive and class cohesion strategies learned during the training program will be encouraged for implementation in the different teaching units of their annual teaching plan. Efforts will be made to ensure that teachers implement them as much as possible, in terms of variety, frequency, and intensity, in each PE class. The experimental group teachers will implement a common set of strategies; however, teachers will have the flexibility to adapt these strategies to their specific educational context, considering the characteristics and needs of their students. This process will be conducted under the supervision of a research team member.

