##### Relatedness-supportive/thwarting behaviors

To assess students’ perception of their teacher’s relatedness-supportive and relatedness-thwarting behaviors in PE lessons, the Teacher Interpersonal Style Questionnaire (TISQ; Leo et al., 2023f) will be used. The scale begins with the stem “In PE classes, my PE teacher …” followed by 24 items (four items per factor). In this study, only the relatedness-support factor (e.g., “…always fosters positive relationships among classmates”) and the relatedness-thwarting factor (e.g., “…creates a classroom atmosphere that I do not like”) will be used. Additionally, to control for the effects of the other two basic psychological needs, one item related to autonomy support (e.g., “…takes our opinions into account when planning lessons”) and one item related to competence support (e.g., “…encourages us to trust in our ability to do things well”) will be included. Responses will be collected using a 5-point Likert scale, ranging from 1 (*strongly disagree*) to 5 (*strongly agree*).

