This study is expected to contribute to new knowledge in 10 key areas: (1) grounded in SDT and CMC, this will be the first teaching program specifically designed to equip teachers with relatedness-supportive/thwarting and class cohesion strategies within an educational context; (2) the quality of the training program will also be assessed using questionnaires, a focus group involving all PE teachers, and observations by an external researcher; (3) the training program will be implemented not only prior to the intervention phase but also during it through a booster sessions; (4) the training program will also include two individual follow-up sessions, during which constructive feedback will be provided, along with individualized debriefings; (5) promising strategies that have demonstrated effectiveness in previous SDT-based training programs will be employed (e.g., supportive attitude, congruent style, concise theoretical input, co-creation of teaching strategies; Vasconcellos et al., 2020; White et al., 2021); (6) intervention fidelity will be evaluated using an observation instrument aligned with both SDT and CMC frameworks; (7) the TMBs identified by Ahmadi et al. (2023) will be applied during the intervention to determine which specific techniques drive its effects; (8) the effects of the intervention on teacher variables will be evaluated using a mixed-methods approach, including questionnaires and focus group; (9) the differential effects of the intervention on male and female students —and, if feasible, on teachers— will be examined; and (10) a follow-up post-intervention assessment will be conducted to evaluate the long-term impact on the study variables. These 10 key aspects will help future PE researchers and teachers replicate the training program and its implementation in other educational contexts, ensuring its adaptability and feasibility within typical school settings.

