### Limitations

This intervention faces certain limitations that should be considered. Firstly, although the first part of the training program can be considered brief to ensure that PE teachers effectively integrate these techniques into their PE classes, an excessively long duration could discourage their participation. Nevertheless, a booster session will be scheduled 3 months after the first two sessions of the training program. Secondly, to avoid overburdening students, we will assess their perceptions of teachers’ autonomy- and competence-supportive/thwarting behaviors with a single item to control for its effects in the analysis, which may limit our ability to fully gauge their impact. In contrast, teachers will complete the full set of items for both need-supportive and need-thwarting behaviors to control for these effects in the analysis. Thirdly, while students’ perceptions of class cohesion will be measured using a validated scale (Leo et al., 2023c), we were unable to assess class cohesion support, understood as the specific teacher behaviors aimed at promoting task cohesion (e.g., “The teacher encourages us to help each other during the development of tasks and activities) and social cohesion (e.g., “The teacher encourages us to participate together in activities outside of class.”). Fourthly, to assess the fidelity of the intervention, only two classes will be randomly observed for each experimental group teacher due to a lack of human resources. Finally, although all teachers will receive the same training program, each teacher will need to adapt the strategies to their context, the characteristics of their students, available spaces, material resources, etc. Therefore, the number and intensity of the use of relatedness supportive and class cohesion strategies may vary slightly depending on each group.

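### The design cannot show which techniques drive the effect, and the promised control for autonomy and competence support names no measurement wave, so post-training values could enter as covariates

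*Protocol article*

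**What the plan says.** **Techniques.** Item (7) of the contributions listed in the Discussion says the teacher motivational behaviors "will be applied during the intervention to determine which specific techniques drive its effects". Under PE implementation for experimental group students, "The experimental group teachers will implement a common set of strategies", which each teacher may adapt to context. Sample recruitment gives 8 to 10 teachers split equally. The control group section limits control participation to questionnaires. Fidelity is tracked by weekly teacher checklists and by two observed classes, which Limitations places with the experimental teachers. The Plan of analysis relates no technique to any outcome.

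**Autonomy and competence.** For teachers, the section on interpersonal behavior says "we will also include autonomy- and competence-supportive/thwarting behaviors to control for their potential effects". For students, one autonomy-support and one competence-support item are added "to control for the effects of the other two basic psychological needs". Limitations repeats that students are assessed "with a single item to control for its effects in the analysis". Measures has the instruments given at T1, T2 and T3. The Plan of analysis names only background covariates (age, sex, school or sociocultural variables and the like), offered as examples, and does not mention autonomy or competence behaviors.

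**Scope.** The review of previous programs says "the present study focuses specifically on relatedness support" and that "the specific contribution of relatedness support strategies to students’ learning remains largely unexplored". It then says the gap is met by joining the relatedness and cohesion frameworks.

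**The concern.** Two statements about what the trial will show go further than the design allows, or leave room for an analysis that would damage it.

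First, finding out which technique produced an effect requires techniques that vary by design, or at least enough teachers and records to relate use to outcome. Neither is present, so a report that follows item (7) literally would make causal statements about techniques from a handful of self-selected patterns of use.

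Second, a covariate measured after training may itself be a result of training. The class cohesion section mentions, as possible strategies, "assigning interdependent roles, responsibilities, and tasks, as well as promoting peer communication, peer assessment with formative purposes", and opportunities for students to voice interests and concerns. The student autonomy item asks whether the teacher considers their opinions in planning lessons. Some spillover from the package to perceived autonomy or competence support is therefore plausible. If T2 or T3 values of these variables are held fixed, part of the program's own effect is removed, and students who are no longer comparable are compared across arms. With the wave left open, the choice could also be made after results are seen.

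**Working it through.** The protocol gives no figure for either point. The effect sizes below are assumptions; the teacher numbers and the 0.05 threshold come from the protocol.

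**1. Technique attribution**

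- Trained teachers: 8/2 = 4 to 10/2 = 5.
- Smallest correlation significant at two-sided 0.05 between one technique's use and a teacher-level outcome: r = t/√(t² + df), with df = n − 2.
- n = 4: df = 2, t = 4.303, r = 4.303/√(18.52 + 2) = 0.950.
- n = 5: df = 3, t = 3.182, r = 3.182/√(10.13 + 3) = 0.878.
- Keeping one residual degree of freedom, at most n − 2 = 2 or 3 techniques fit in one model.
- This is before any multiplicity correction, and such associations would not be randomized.
- The same limit applies to components. Relatedness and cohesion strategies are both present in one arm and both withheld from the other. A model with an intercept, a relatedness indicator and a cohesion indicator therefore has rank 2 of 3, and randomization cannot separate the two.

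**2. Adjusting for autonomy or competence support**

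With one covariate and equal slopes in both arms, adjusted coefficient = total effect − s × a. Here a is the shift that training causes in the covariate and s is the within-arm slope of the outcome on it. At T1, before implementation, a has expectation zero by randomization, so nothing is systematically subtracted.

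Simple example (assumed): total effect 0.30 SD, a = 0.20 SD, s = 0.6. Adjusted = 0.30 − 0.6 × 0.20 = 0.18 SD, a loss of 0.12/0.30 = 40%. Over s = 0.4 to 0.7 and a = 0.1 to 0.3 the loss runs from 0.4 × 0.1 = 0.04 SD (13%) to 0.7 × 0.3 = 0.21 SD (70%). If a = 0 the loss is zero.

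Structured example (assumed): τ is the package effect that bypasses the covariate, b the covariate's effect on the outcome, and h the loading of a shared reporting tendency on both. The covariate has within-arm variance 1, so total = τ + ab and s = b + h².

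| τ | a | b | h | Total effect | T1-adjusted | Post-training-adjusted |
|---|---|---|---|---|---|---|
| 0.3 | 0.5 | 0.3 | 0 | 0.45 | 0.45 | 0.45 − 0.30 × 0.5 = 0.30 |
| 0.3 | 0.5 | 0.3 | 0.5 | 0.45 | 0.45 | 0.45 − 0.55 × 0.5 = 0.175 |
| 0 | 0.5 | 0.3 | 0.5 | 0.15 | 0.15 | 0.15 − 0.55 × 0.5 = −0.125 |
| 0.3 | 0 | 0.3 | 0.5 | 0.30 | 0.30 | 0.30 |

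A simulation with 2,000,000 units returned 0.300, 0.176, −0.126 and 0.302 in the last column. With a shared reporting tendency, the post-training-adjusted coefficient does not recover the direct effect τ either: it gives 0.175 where τ = 0.3, and an apparent harm where τ = 0.

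**The case against.** The strongest reply is that the main comparison is untouched as written. Hypotheses 1, 2 and 4 set the program against no training, and the aims name a combined relatedness-plus-cohesion program throughout. Several stronger readings do not hold:

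- **That the trial claims to isolate relatedness support.** A reader might infer this from the stated focus and the gap described, but the protocol does not say it. The remark about isolation concerns earlier strategies, and the next step is an open combination of two frameworks.
- **That post-training values will be adjusted for.** No section says so. T1 values exist, teachers complete T1 before the frameworks are introduced, and the covariates that are named are background characteristics. Use of T1 is an equally available reading.
- **That the Plan of analysis contradicts the measures sections.** Its covariate list is given as examples, so an unnamed variable is unreconciled, not excluded.
- **That the training raises autonomy or competence support.** The strategies cited are background possibilities, and the actual content is co-created with teachers. Spillover is plausible but not stated, and without it the adjustment costs nothing.

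Item (7) is also a single Discussion sentence tied to no hypothesis. Teachers may adapt the strategies, so checklists and observations will yield some variation to describe. The critical correlations refer to an analysis the protocol does not plan and serve only to show how little 4 to 5 teachers could support.

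All of this narrows the point without removing it. Item (7) still promises something the design lacks. The promise to control for autonomy and competence is made in three places, one of them explicitly for the analysis, and an analyst following it could choose a harmful wave.

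**Conclusion.** The concern holds in two limited parts.

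The technique claim is unsupported. With two arms, one common package, 4 to 5 trained teachers and no technique records planned for controls, the trial can describe technique use or explore non-randomized associations, and no more.

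The control for autonomy and competence behaviors is left undefined in a way that matters. Harm is conditional on two things: that T2 or T3 values are used, and that training shifts them. If both hold, the coefficient stops being the program effect of Hypotheses 1, 2 and 4. In the simple assumed example the loss is 0.04 to 0.21 SD on an effect of 0.30 SD. If either fails, the program effect is preserved. The randomized package-versus-control contrast is therefore not invalid as the protocol stands.

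T1 adjustment is safe but does not separate relatedness from the other needs. That question is better addressed by looking at the other needs as outcomes.

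**What to change.** - In Teacher interpersonal behavior, Relatedness-supportive/thwarting behaviors, Plan of analysis and Limitations, state that only T1 values of the autonomy and competence variables enter as covariates, and name them in the covariate list.
- Analyze the T2 values of these variables by arm as specificity outcomes: did the program move relatedness support more than support for the other two needs? For students this rests on single items and should be read with that in mind.
- Reword item (7) of the Discussion to say that the trial will describe which techniques were used and how often, with any link to outcomes labelled exploratory.
- State that conclusions about effects apply to the combined relatedness-plus-cohesion package.

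The cost is wording and one extra between-arm comparison on data already to be collected. The downside is a less ambitious claim.

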##### Relationship satisfaction with students

To assess teachers’ perception of their relationship satisfaction with their students, a single-item measure used in previous studies (Cheon et al., 2020) will be used: “I have a good and satisfying relationship with my students.” Teachers will rate this item on a 10-point Likert Scale, ranging from 1 (*strongly disagree*) to 10 (*strongly agree*).

##### Teacher beliefs

To evaluate teachers’ perceptions of the importance and value of implementing relatedness-supportive and class cohesion strategies during PE classes, the Aelterman et al. (2014) questionnaire will be used. Specifically, this questionnaire has been slightly modified to target relatedness-supportive practices, consisting of four items (e.g., “I believe it is essential for teachers to always promote positive relationships among classmates”). Responses will be assessed using a 5-point Likert scale, ranging from 1 (*strongly disagree*) to 5 (*strongly agree*).

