Therefore, grounded in SDT, the role of teachers in promoting positive socio-emotional classroom climates and shaping students’ interactions is highly significant. However, SDT conceptualizes relatedness as the subjective experience of feeling connected, accepted, and cared for by significant others, and it does not require interaction with the entire peer group for this need to be fulfilled (Deci and Ryan, 2014). That is, a student may satisfy their need for relatedness through a few meaningful relationships, without necessarily feeling integrated into the broader classroom community. This limitation makes it difficult for SDT alone to fully capture group-level dynamics such as class cohesion. Given that Spanish educational policies emphasize active methodologies and peer collaboration, fostering cooperation and positive peer relationships across the classroom is essential to optimize learning. In this context, the concept of class cohesion offers a complementary perspective that focuses on the collective experience of the classroom as a social unit, which has received significantly less attention in educational research (Leo et al., 2023d). Consequently, integrating the CMC allows us to address the theoretical and practical gap left by SDT in capturing the dynamics of peer-to-peer relationships on a class-wide scale.

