#### Aim 2: effects of teacher program on teachers

As for the second objective, most SDT-based training programs in PE have primarily examined their effects on students (Vasconcellos et al., 2020). However, preliminary evidence also suggests that these training programs can be beneficial for teachers as well (Reeve and Cheon, 2021). Thus, using a mixed-method approach, the second aim will be to examine the effects of the training program on teachers’ beliefs, feasibility, and intention to apply relatedness-supportive and class cohesion strategies, use of relatedness-supportive behaviors, and relationship satisfaction with students. In line with this aim, it is hypothesized that, by T2, experimental group teachers will perceive improvement in beliefs, feasibility, and intention to apply relatedness-supportive and class cohesion strategies, use of relatedness-supportive behaviors, and relationship satisfaction with their students, compared to those who do not receive any training (Hypothesis 4). Due to the scarcity of prior research, we will not posit specific hypotheses about the intervention’s long-term (T3) effects on the study variables. If enough male and female teachers participate in the training program, the intervention’s effects on the study variables will also be examined by sex.

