##### Feasibility of teaching strategies

To evaluate teachers’ perceptions of the feasibility of implementing relatedness-supportive and class cohesion strategies, the same set of items used to measure their teaching beliefs (e.g., “It is feasible for teachers to foster positive relationships in the classroom”; Aelterman et al., 2014) will be applied. Responses will be assessed using a 5-point Likert scale, ranging from 1 (*totally unfeasible*) to 5 (*totally feasible*).

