##### Intention to apply teaching strategies

To evaluate teachers’ intention of implementing relatedness-supportive and class cohesion strategies, the same four-item scale used to assess their pedagogical beliefs will be employed (e.g., “I will promote positive relationships among classmates”; Aelterman et al., 2014). Responses will be assessed using a 5-point Likert scale, ranging from 1 (*no intention*) to 5 (*definite intention*).

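### Teacher beliefs, feasibility and intention are named for relatedness and class cohesion strategies, but the four items they share are described as targeting relatedness support, so a result on them cannot speak to cohesion strategies

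*Protocol article*

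**What the plan says.** Under Aim 2, Hypothesis 4 predicts that by T2 "experimental group teachers will perceive improvement in beliefs, feasibility, and intention to apply relatedness-supportive and class cohesion strategies", relative to untrained teachers. The closing part of the Discussion and the Conclusion repeat the same joint construct.

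In Teachers' measures, the Teacher beliefs entry gives its purpose as assessing "perceptions of the importance and value of implementing relatedness-supportive and class cohesion strategies during PE classes". The entries on feasibility and on intention also name both kinds of strategy.

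The content of the instrument is described once, under Teacher beliefs: "this questionnaire has been slightly modified to target relatedness-supportive practices, consisting of four items". Feasibility is then measured with "the same set of items used to measure their teaching beliefs", and for intention "the same four-item scale used to assess their pedagogical beliefs will be employed". No cohesion item or cohesion subscale is described under any of the three.

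**The concern.** Cohesion is in the stated purpose of all three scales but is absent from the one sentence that says what their items target. If that sentence is accurate, the scores are mainly scores for relatedness support under a broader label.

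Cohesion is one of the two halves of the programme and part of what the protocol presents as new. A favourable result on these outcomes would be reported as a gain in teachers' beliefs, perceived feasibility and intention about cohesion strategies, when it might come wholly from the relatedness half. A null result would be read as no effect on cohesion strategies, when those strategies had no score of their own.

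**Working it through.** The plan gives no figure to reproduce. The check is a count and a comparison of the text.

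**1. Which outcomes are affected.** Aim 2 lists the Hypothesis 4 outcomes as "beliefs, feasibility, and intention to apply relatedness-supportive and class cohesion strategies, use of relatedness-supportive behaviors, and relationship satisfaction with their students". That is five: beliefs, feasibility, intention, relatedness-supportive behaviour and relationship satisfaction. Cohesion is attached to the first three only, and those three share the four items. The count affected is 3 of 5.

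**2. Purpose against item content.**

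| Outcome | Stated purpose | Described item content | Example item shown |
|---|---|---|---|
| Beliefs | Both kinds of strategy | Four items aimed at relatedness support | Promoting good relationships among classmates |
| Feasibility | Both kinds of strategy | Same items | Fostering good relationships in the classroom |
| Intention | Both kinds of strategy | Same four items | Promoting good relationships among classmates |

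The three examples look like a single item under three stems, so probably one of the four items is visible.

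**3. How the protocol classifies the visible wording.** The belief example is "I believe it is essential for teachers to always promote positive relationships among classmates". In the students' measures, almost the same wording, with the teacher as subject, is the example for the relatedness-support factor of the teacher interpersonal style questionnaire. In the protocol's own scheme it is therefore a relatedness-support item. The section on class cohesion, however, defines social cohesion in terms of bonds among students, and the item overlaps with that. Task cohesion is defined there as collaboration on academic work, with strategies such as interdependent roles and shared goals. The visible wording touches none of this.

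**4. Whether the protocol treats the two constructs as interchangeable.** It does not. It introduces the cohesion model because relatedness can be satisfied through a few relationships without class-wide integration: "This limitation makes it difficult for SDT alone to fully capture group-level dynamics such as class cohesion". That sentence is about students' experience rather than teachers' attitudes. It is background for keeping the constructs apart, not direct evidence about the teacher items.

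**5. Whether another source supplies the comparison.** Hypothesis 4 needs experimental and control teachers compared.

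- The focus group covers cohesion strategies, but only qualitatively, only at T2 and only with experimental teachers.
- The weekly checklists and observations record cohesion techniques used, not beliefs, feasibility or intention. Control teachers take part only by completing questionnaires.
- The students' class cohesion scale is given in both arms, but it measures students' perceptions of their class.
- The Limitations section admits that teachers' cohesion-supporting behaviour could not be assessed, in a point about student measures. It does not mention beliefs, feasibility or intention.

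**The case against.** The strongest reply is that most of the form is unseen. An article usually prints one example per scale, and the full item list may stand elsewhere with cohesion content in it. The text speaks of a slight modification, the visible item overlaps with social cohesion, and the protocol's account of relatedness support itself includes exchanges among students and group integration. Aim 2 is also mixed-method, with cohesion strategies covered in the focus group and the checklists.

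Much of this stands, and it rules out some stronger readings. A reader might infer that the scores cannot move at all when attitudes to cohesion change, or that the items concern relatedness exclusively. The documents do not show either: three of the four items are probably not shown, and the visible one could pick up some change in social cohesion. A reader might also count all five Hypothesis 4 outcomes as failing to measure cohesion. That is unfair to two of them, since the hypothesis never claims that relatedness-supportive behaviour or relationship satisfaction measures it. Nor can the loss be put in scale points without assuming item content and weights that the protocol does not give.

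The reply does not remove the core. The point relies on what the article affirms about the target of the items, not on a missing item list. If cohesion items exist, the description under Teacher beliefs is incomplete. If they do not, the purpose statements and Hypothesis 4 claim too much. The text needs correcting in either case, and the mixed-method sources have no control arm.

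**Conclusion.** The concern holds as a mismatch between stated construct and described items, for three of the five Hypothesis 4 outcomes. As described, a controlled result on beliefs, feasibility or intention cannot be attributed to class cohesion strategies: there is no separate cohesion score, and nothing shown covers task cohesion. Partial coverage of social cohesion is possible.

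This assumes that the single description of the item target is accurate and applies to all three stems, as the protocol says it does. The size is a count, not a bias in score units. The matter should be corrected, but its reach is limited: these scales are completed by 8–10 teachers in all, and the student outcomes do not depend on them.

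**What to change.** **Preferred, before T1.** Under each of the three stems, add two to four parallel items on task- and social-cohesion strategies, for example interdependent roles and shared goals. If such items already exist among the four, identify them. Report relatedness and cohesion subscores separately and state Hypothesis 4 for each. Two to four items under three stems adds 6 to 12 ratings (2 × 3 to 4 × 3) to the present 12 (4 × 3), on a form of about 15 minutes. The downside is a slightly longer form and items without prior validation.

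**Otherwise.** Limit Hypothesis 4, the entries for beliefs, feasibility and intention, the closing part of the Discussion and the Conclusion to relatedness-supportive strategies. State that teachers' views of cohesion strategies are examined only qualitatively, in experimental teachers, and add the gap to the Limitations. This costs only wording and remains possible if baseline data have already been collected.

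Neither option changes the design, the sample or the assessment schedule.
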